### Additional Measures

Additional measures of mainly psychological variables will be collected in order to use them as possible explanatory variables of the primary or secondary efficacy measures. Moreover, usability, fidelity, and data extracted from the phone database will be collected for validation purposes.

Physical activity behavior. Self-reported data regarding participants’ current physical activity behavior as recorded with the International Physical Ativity Questionaire (IPAQ) [53] will be collected at -*t*
_2_ and -*t*
_1_ and at weeks *t*
_7_ and *t*
_8_. Self-reported physical activity behavior through self-reports, before the quit day at -*t*
_2_ and -*t*
_1_, will be verified by measuring their step counts (via pedometer Omron HJ-152) the last week before measurement day. IPAQ records the physical activity of 4 intensity levels for the last 7 days: (1) vigorous-intensity activities such as aerobics, (2) moderate-intensity activities such as leisure cycling, (3) walking, and (4) sitting.Relapse situation efficacy as recorded with the Relapse Situation Efficacy Questionnaire (RSEQ) [54] will be assessed before the quit day at -*t*
_2_ and -*t*
_1_. RSEQ consists of 75 simple items assessing participants’ confidence in their ability to resist the temptation to smoke in a wide variety of contexts. A 4-point response scale is used from 1(not at all confident) to 4 (extremely confident).Attitude toward, intention to, and perceived behavioral control of increasing physical activity behavior will be measured through a self-reported questionnaire before and after quit day at -*t*
_2_ and *t*
_1_. Similarly, attitude toward, intention to, and perceived behavioral control of quitting smoking will be measured before quit day at -*t*
_2_. Likewise, attitude toward, intention to, and perceived behavioral control of craving management will be measured during the fourth session at *t*

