### Statistical Methods

Generalized linear mixed models will be used to examine differences between the groups on the dichotomous primary outcome variable: abstinent versus smoker status at the 6-month follow-up time point (ie, *t*
_8_). The differences at all follow-up time points will also be examined, but the 6-month follow-up is considered to be the primary focus. Descriptive statistics will be used to report process data. Any covariates identified in the preliminary analyses will be added to the model. Linear mixed models will be used to analyze the secondary efficacy measures for data that are normally distributed or are approximate to a normal distribution (via data transformations). For count variables, a generalized Poisson mixed model will be applied. Alternatively, we will use nonparametric tests by time point separately.

Finally, 3 separate logistic regressions on the primary dichotomous outcome (abstinent-smoker) will be performed using the theory of planned behavior (TPB) constructs of quit smoking behavior and increased physical activity behavior at the -*t*
_2_ time point and the TPB constructs of manage cravings behavior at the *t*
_1_ time point as predictors. Linear regressions for the continuous variables of the secondary efficacy outcomes will be used to test the predictive ability of all TPB constructs. All analyses will be conducted using intent-to-treat principles with participants remaining in their originally assigned groups after randomization regardless of adherence or protocol deviation. This is done to increase the likelihood that group differences are due to the intervention and unaffected by biases that lead to an overestimation of the intervention effect [56].

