### Power

We determined the power for our primary hypothesis, which stated that the 7-day PPA at the 6-month follow-up would be higher in the experimental group than in the comparator group. In order to detect a difference of 10% in quit rates between the experimental and comparator groups, with an expected quit rate of 25% in the comparator group, the study would require, at 80% power with a two-sided *p* value of 0.05, a sample size of 326 participants. Given the budget and time limitations as well as the location (eg, a small city in a sparsely populated area, which makes recruitment a challenge), a sample size of 50 has been set by the research group as a more realistic number when taking into account the available resources. Given the sample size of 50 participants equally assigned to the groups, we calculated the smallest PPA that we could detect with power greater than 0.80. Assuming that the abstinence in the comparator group will be 25% [1-3], power analysis through online calculations [57] indicate that we will be able to detect a significant difference between the experimental and comparator groups with power greater than 0.80 if the PPA in the experimental group is 59% or higher. The percentage of 59% required to obtain statistical power is considered to be very high. At the end of the study we will re-estimate the power of the final percentage differences between groups in the effectiveness report, depending on the exact final sample size as well. Nevertheless, the sample size is considered as an a priori limitation to the study.

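### With about 12 to 21 abstainers among 50 people, the three TPB logistic regressions would overstate any real log odds ratio by about 15-27%

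*Protocol article*

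**What the plan says.** Two sets of regressions on the theory of planned behavior (TPB) constructs are planned under Statistical Methods.

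- Logistic, one model per behavior: "3 separate logistic regressions on the primary dichotomous outcome (abstinent-smoker) will be performed using the theory of planned behavior (TPB) constructs". The constructs for quitting and for physical activity are taken at -t2, and those for managing cravings at t1.
- Linear, for the secondary outcomes: "Linear regressions for the continuous variables of the secondary efficacy outcomes will be used to test the predictive ability of all TPB constructs".

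Additional Measures lists three constructs per behavior (attitude, intention, perceived behavioral control) and collects them "in order to use them as possible explanatory variables of the primary or secondary efficacy measures".

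The numbers that fix the information available are under Power: "Given the sample size of 50 participants equally assigned to the groups", "with an expected quit rate of 25% in the comparator group", a 10-point difference as the target effect, and adequate power only "if the PPA in the experimental group is 59% or higher". Participant Retention counts anyone lost to follow-up as a smoker.

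The article states no number of abstainers for the TPB models, no estimator beyond logistic regression, and no measure of fit.

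**The concern.** The precision and bias of a logistic model depend on the number of people in the rarer outcome group, here the abstainers, more than on the total of 50. With few events per predictor, maximum likelihood pushes slopes away from zero on average. An odds ratio for, say, intention would then be reported as stronger than it is.

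The article's warning about the small sample does not cover this. Power and Discussion present sample size as a threat to power, which alerts a reader to missed effects. Small-sample bias in the slopes works in the other direction, towards effects that look too large. What is at stake is how strongly the trial appears to link TPB constructs to abstinence. The answer on the app itself is not at stake.

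**Working it through.** **The plan's own figure.** None is given for the TPB regressions, so there is none to reproduce. The 59% from Power is used here only as an abstinence rate. (With 25 per arm and a two-sided 0.05 test, 25% against 59% gives power of about 0.69 pooled or 0.74 unpooled, not 0.80. That is a separate matter and plays no part below.)

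**Step 1: abstainers.** Formula: 25 × (comparator rate) + 25 × (experimental rate), then divided by 3 constructs.

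- No effect, 25% and 25%: 6.25 + 6.25 = 12.5, or 4.2 per construct.
- Target effect, 25% and 35%: 6.25 + 8.75 = 15, or 5 per construct.
- Detectable effect, 25% and 59%: 6.25 + 14.75 = 21, or 7 per construct.

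These correspond to overall abstinence of 25%, 30% and 42%. Counting dropouts as smokers cannot add abstainers.

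**Step 2: bias of the slopes.** Simulation with 50 people and three standardised predictors, 2,000 to 2,500 datasets per setting. The true odds ratios (per SD) and the correlations are assumptions. The odds ratio shown is the exponential of the mean log odds ratio.

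| Abstinent | True OR (log) | Constructs with effect | Correlation | Mean log OR, maximum likelihood | Excess | OR (excess) | Mean log OR, Firth |
|---|---|---|---|---|---|---|---|
| 25% | 1.5 (0.405) | 1 | 0.3 | 0.468 | 15% | 1.60 (7%) | 0.406 |
| 25% | 2 (0.693) | 1 | 0.3 | 0.801 | 16% | 2.23 (11%) | 0.689 |
| 25% | 2 (0.693) | 1 | 0.5 | 0.843 | 22% | 2.32 (16%) | 0.723 |
| 25% | 2 (0.693) | 3 | 0.5 | 0.880 | 27% | 2.41 (20%) | 0.712 |
| 25% | 3 (1.099) | 1 | 0.3 | 1.283 | 17% | 3.61 (20%) | 1.082 |
| 30% | 2 (0.693) | 1 | 0.3 | 0.815 | 18% | 2.26 (13%) | 0.709 |
| 42% | 2 (0.693) | 3 | 0 | 0.804 | 16% | 2.24 (12%) | 0.698 |
| 42% | 2 (0.693) | 3 | 0.5 | 0.838 | 21% | 2.31 (16%) | 0.709 |
| 25% | 1 (0) | 0 | 0.3 | 0.002 | none | 1.00 | 0.001 |

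At a true odds ratio of 2 and 25% abstinent, the median estimated odds ratio is 2.14 to 2.22, an excess of 7-11%. With 500 people (25% abstinent, one effect, correlation 0.3) the mean log odds ratio is 0.700 against 0.693, an excess of 1%, so the bias comes from the sample size.

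A separate run with correlation 0.4 and true log odds ratios of 0.70 and 0.40 gave maximum-likelihood means of 0.81 and 0.47 at 25% abstinent, against 0.69 and 0.40 by Firth. The root mean squared error of the first slope was 0.59 and 0.47 respectively, so the penalised estimate is also closer to the truth overall.

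**Step 3: apparent fit when nothing predicts.**

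- Logistic: mean apparent AUC is 0.65 at 25% abstinent and 0.63 at 42%. In new samples it is 0.50.
- Overall likelihood-ratio test under noise at 25% abstinent: rejects in about 6-7% of datasets, close to nominal.
- Linear: expected R-squared is p/(n − 1). With three constructs, 3/49 = 0.06. If all nine constructs entered together, 9/49 = 0.18. If the physical-activity constructs at both -t2 and t1 were included, 12/49 = 0.24.

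**The case against.** The strongest reply is that this is a condensed article. It names no AUC, R-squared or other criterion of success, and it does not exclude penalisation or internal validation. Those details commonly sit in a full plan, and their absence is no fault. That stands. The point rests only on what is fixed: logistic regression, three constructs per model, 50 people and the stated rates. If the full plan already specifies a penalised fit, the bias in the slopes is dealt with.

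Several stronger readings are tempting and are not supported.

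- A reader might infer that the protocol judges all these models by predictive fit. The aim to "test the predictive ability of all TPB constructs" belongs to the linear regressions only; the logistic sentence merely uses the constructs as predictors, and Additional Measures calls them explanatory.
- A reader might infer that the odds ratios themselves are inflated by a fifth, even from noise. A figure of that size belongs to the log odds ratio; the odds ratio rises less in most settings, and there is no average inflation when there is no association.
- A reader might infer that noise alone would pass as prediction. The overall test holds close to its level. At least one of three Wald tests is significant in 12-13% of null fits, but that is multiplicity. Only apparent AUC or R-squared read at face value would mislead.
- A reader might take 12 abstainers as the protocol's expectation. That applies the comparator's 25% to both arms; the other scenarios give 15 and 21. The bias persists across all three.
- A reader might take the linear models to hold 9 or 12 constructs at once. The text leaves this open, and the logistic models are separated by behavior.

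It is also fair that none of the five hypotheses under Trial Aim concerns TPB constructs.

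**Conclusion.** The point holds as a small-sample bias in ancillary analyses. With about 12 to 21 abstainers and three constructs per model, ordinary maximum likelihood would overstate a real log odds ratio by about 15-27%, roughly 7-20% on the odds ratio. The event counts follow from the protocol's rates. The size of the bias rests on assumed odds ratios of 1.5 to 3 per SD, assumed correlations of 0 to 0.5, and the usual reading of logistic regression as maximum likelihood. The optimism in AUC and R-squared is conditional on their being reported uncorrected. The comparison of the app group with the comparator does not depend on these models. The consequence is modest, but the remedy costs so little that the change is worth making.

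**What to change.** In Statistical Methods, state that:

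- the three logistic regressions on TPB constructs are fitted by Firth penalised likelihood;
- the linear regressions enter one behavior's three constructs at a time, as the logistic models already do;
- any AUC or R-squared reported for these models is given with a bootstrap optimism-corrected value;
- these results are exploratory, with the number of abstainers shown beside each logistic model.

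This needs no new data, only a change of wording and a few lines of code. The price is that associations and any prediction figures will look less favourable. Firth estimation removes most of the bias but adds no information: intervals from 12 to 21 abstainers will stay wide.

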### Recruitment, Randomization, and Allocation

Recruitment will occur through referrals from the health care units in the Jyväskylä area as well as via the Web pages of Central Finland Respiratory Association, the City of Jyväskylä, Radio Jyväskylä, and Yle News. All interested participants will be screened for eligibility. The enrollment period ended in May 2015. The first 50 eligible participants will start the smoking cessation intervention, which consists of 3 weekly counseling sessions and will help them set a quit date. The rest of the eligible participants will be put on a waiting list and invited to participate in case of dropouts before the quit day/randomization time point. The first 50 participants to reach the quit day/randomization time point will then form the intention-to-treat group that will continue in the study. After the quit day/randomization, participants will be assigned to an experimental group (25 participants) and a comparator group (25 participants), and both groups will separately have 1 more counseling session on how to manage cravings. In this fourth session, the only difference in treatment between the groups is that the experimental group will have an extra 10-15 minutes of guidance on how to use the Ph.o.S app to manage cravings during the follow-up period. Both groups will be followed up for the main and secondary efficacy outcomes of interest for 6 months. The method of randomization is a set of numbers generated by online software [38]. The principal investigator will generate the allocation sequence and the study nurse will assign participants to the groups. The study nurse is blind to the allocation sequence until the third session and the principal investigator is blind to the participants and their data up to the first follow-up measure.

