_1_. Attitude toward all 3 behaviors (ie, increasing physical activity, quitting smoking, and managing cravings) is assessed with 6 items using a 7-point semantic differential scale (ranging from -3 to +3): ‘‘To (behavior) in the following month will for me be...’’: good-bad, unpleasant-pleasant, wise-silly, easy-difficult, healthy-unhealthy, important-not important. Similarly, intention is measured with 3 items: “In the following month...”: (1) “I intend to (behavior),” (2) “I will try to (behavior),” (3) “I plan to (behavior).” Answers are given on a 7-point scale ranging from 1 (very likely) to 7 (very unlikely). Correspondingly, perceived behavioral control is measured with 4 items, for example: “For me to (behavior) in the next month is...,” and rated on a 7-point scale, with participants answering from 1 (easy) to 7 (difficult).Usability of the Ph.o.S app for the experimental group only will be collected through the System Usability Scale (SUS) self-reported questionnaire [55] 1 week (*t*
_3_) and 1 month (*t*
_6_) after participants have started using it. SUS is a 10-item scale giving a global view of subjective assessments of usability. Answers are given on a 5-point scale from 1 (strongly agree) to 5 (strongly disagree). Moreover, a follow-up qualitative assessment when the user stops using the app is performed in order to determine the reasons for discontinuation and possible other means they use to manage cravings effectively.All participants are asked fidelity check questions during the follow-up measure at *t*
_2_, *t*
_3_, *t*
_6_, *t*
_7_, and *t*
_8_. Questions are related to additional help (eg, pharmacological, mHealth apps) used to manage cigarette cravings. Additional questions for the experimental group are related to the ways they use the Ph.o.S app.Information from the Ph.o.S app is also collected constantly during the follow-up period for the experimental group from the time they start using it (*t*
_2_-*t*
_8_). Data, such as frequency of use and frequency of successful and unsuccessful efforts to manage craving through the suggested solutions, will be extracted and used to verify the corresponding self-reported questions. Additional data will be extracted for descriptive purposes.

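### The regressions on constructs measured at the fourth session list no arm term, although those constructs are taken after allocation and in arm-separate sessions

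*Protocol article*

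**What the plan says.** All references are to the protocol article.

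- **Models.** Statistical Methods plans that "3 separate logistic regressions on the primary dichotomous outcome (abstinent-smoker) will be performed using the theory of planned behavior (TPB) constructs". Two models take their constructs (quitting smoking, increasing physical activity) from -t2, and the third takes its constructs (managing cravings) from t1. Linear regressions of the continuous secondary outcomes then test all the constructs, with no time point given. The sentence on adding covariates stands in the preceding paragraph, with the mixed model for the primary outcome. The intention-to-treat sentence says which group a participant counts in, not which terms a regression holds.
- **Outcome.** The dichotomous outcome is "abstinent versus smoker status at the 6-month follow-up time point", that is t8.
- **Timing of the constructs.** Additional Measures states that "perceived behavioral control of quitting smoking will be measured before quit day at" -t2, and that "perceived behavioral control of craving management will be measured during the fourth session at" t1. The physical-activity constructs are measured at both -t2 and t1.
- **Allocation.** Under Recruitment, Randomization, and Allocation: "After the quit day/randomization, participants will be assigned to an experimental group" or a comparator group. Each group then has its own fourth session, and the experimental one adds 10 to 15 minutes on using the app against cravings.
- **Item wording.** Attitude items begin "To (behavior) in the following month will for me be", and a perceived-control item begins "For me to (behavior) in the next month is".

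**The concern.** A predictor measured after allocation can itself be moved by allocation. In Trial Aim the main hypothesis is that the app raises abstinence, and further hypotheses are that it raises self-efficacy and power of control over cravings. Perceived control of craving management at t1 is close in content to those scores. If arm raises both the construct and the outcome, the two are correlated across the whole sample even when they are unrelated within each arm. A regression without arm would then report the construct as a predictor of abstinence, when part or all of the association is the treatment effect.

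The same holds for any linear regression on t1 constructs, because its outcomes are the craving scores that the trial expects to differ by arm. For power of control there is a further route: Secondary Efficacy Measures shows an example item worded differently in the two arms, so arm may shift that score through the wording alone.

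At stake is the reading of a supplementary analysis: a claim that a psychological construct predicts staying abstinent.

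**Working it through.** **1. Order of events.** Session 1 (-t2), session 3 (-t1), quit day and allocation (t0), session 4 held separately by arm (t1), then follow-up to t8, 24 weeks after t1. Constructs from -t2 precede allocation, so arm is independent of them except by chance and leaving it out does not confound those two logistic models. Constructs from t1 follow allocation.

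**2. Inputs.** The plan has no figure of its own on this point to reproduce. From the Power section: 25 per arm, comparator abstinence 25%, experimental abstinence 35% (the 10-point difference) or 59%. Assumed: 45% as a middle case, and an arm shift d of 0.5 to 0.8 SD in the construct.

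**3. Approximation by hand.** Let the construct be x = d × arm + noise with SD 1, and let abstinence depend on arm only, with difference Δ and mean rate p. With equal arms:

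r = (dΔ/4) / [√(1 + d²/4) × √(p(1 − p))], z = r√48 / √(1 − r²), rejection rate = Φ(z − 1.96) + Φ(−z − 1.96).

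Example, 25% v 59% and d = 0.8: r = (0.8 × 0.34/4) / (√1.16 × √(0.42 × 0.58)) = 0.068 / (1.077 × 0.494) = 0.128. Then z = 0.89 and the rate is about 0.143 + 0.002, or 15%.

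**4. Simulation.** 3,000 to 4,000 trials per case, one construct, likelihood-ratio test at 0.05:

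| Abstinence | d (SD) | r | By hand, no arm | Simulated, no arm | Simulated, with arm |
|---|---|---|---|---|---|
| 25% v 35% | 0.5 | 0.027 | 5% | about 6% | about 6% |
| 25% v 35% | 0.8 | 0.041 | 6% | about 6% | about 6% |
| 25% v 45% | 0.5 | 0.051 | 6% | 7% | 6% |
| 25% v 45% | 0.8 | 0.078 | 8% | 10% | 6% |
| 25% v 59% | 0.5 | 0.084 | 9% | 9 to 10% | 6% |
| 25% v 59% | 0.8 | 0.128 | 15% | 16% | 6% |

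Repeat runs agree to about one percentage point; the simulation standard error near 6% is √(0.06 × 0.94/3000) = 0.4 points. With 50 participants the likelihood-ratio test runs slightly above 5% even with arm in the model. The Wald test runs lower, with the same pattern. Without v with arm it gives 4.6% v 4.4% (d = 0.5) and 4.9% v 4.1% (d = 0.8) at 25% v 35%, and 8.0% v 4.3% and 12.9% v 4.1% at 25% v 59%.

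**5. Linear regressions.** With an outcome shift of e SD, r = (de/4) / [√(1 + d²/4) × √(1 + e²/4)].

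- d = e = 0.5: r = 0.0625/1.0625 = 0.059, z = 0.41, rate about 7%.
- d = e = 0.8: r = 0.16/1.16 = 0.138, z = 0.97, rate about 16%.

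Simulation gives the same 7 to 16%, against 5% with arm.

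**6. Horizon of the items.** A month asked about at t1 ends near t6 (4 weeks after t1), so 24 − 4 = 20 of the 24 weeks to t8 lie beyond it. For -t2: session 3 is 2 weeks after session 1, the quit day 0 to 1 week later (assumed), and session 4 up to 1 week after that. Session 4 is thus 2 to 4 weeks after -t2, and the -t2 month ends 0 to 2 weeks after session 4, which is 2 to 4 weeks before t6.

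**The case against.** The strongest answer is that the article never says that the arms are pooled or that arm is left out. It lists the constructs in one sentence of a condensed paper, and further model terms may be in an analysis plan that is not shown. That stands as far as it goes. A reader might infer a stated decision to pool, and the documents do not support that. What can be said is that the list of predictors as printed holds no arm term, and that neither the covariate sentence nor the intention-to-treat sentence supplies one.

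Second, a reader might extend the concern to all three logistic models. That fails, because two of them use answers given before randomization.

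Third, the arm shift at t1 is unknown. The article says that the form is completed during session 4, not whether this comes before or after the app guidance, and daily use of the app has not begun. This stands: with no shift there is no inflation. At the protocol's own 25% v 35% there is almost none even with a shift of 0.8 SD, and the Power section itself regards 59% as very high.

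Fourth, a reader might call the one-month item wording against a t8 outcome an error. It is a choice. Whether short-horizon attitudes predict six-month abstinence is a fair question, and t8 is cotinine-verified whereas t6 is self-report only. Moving the outcome to t6 would not match the -t2 items either, as step 6 of the working shows.

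**Conclusion.** The concern holds for the logistic regression on the t1 craving-management constructs and for any linear regression on t1 constructs. As printed, these models can let a treatment effect pass for a construct effect. The excess of false positives runs from almost nothing at 25% v 35% to about 10 percentage points at 25% v 59% with a 0.8 SD shift (16% against about 6%).

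These sizes rest on the assumed shift of 0.5 to 0.8 SD, on a construct with no relation to the outcome inside either arm, and on a single construct in the model, whereas the planned models hold several. They show what could happen and do not predict what this trial will find.

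The point is minor. These are supplementary explanatory analyses, and neither the primary comparison of the arms nor the secondary efficacy comparisons depend on them.

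**What to change.** 1. State that arm enters the logistic model on the t1 craving-management constructs and every linear regression that uses t1 constructs. The -t2 models do not need it to remove bias.
2. Describe the t1 constructs as measured after allocation, and report whether the form was completed before or after the app guidance. Follow-up had already begun when the article was written (Trial Status), so re-ordering the session is no longer a practical remedy.
3. Optionally, report t6 abstinence as a sensitivity outcome for the t1 regression only, since its items ask about the coming month. Keep cotinine-verified t8 as the main outcome and label t6 as self-reported.

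The cost is a few lines of analysis text and no new data. The arm term uses one parameter in a small model. At 25% v 35% about 25 × 0.25 + 25 × 0.35 = 15 abstainers are expected, so a model with three constructs goes from 15/3 = 5 to 15/4 = 3.75 abstainers per term. The estimates will be imprecise either way and should be reported as exploratory.
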